## Interventions

### Explanation for the choice of comparators {6b}

The comparator devices selected for this study are non-IP-coated acetabular revision cups, acetabular augments, and revision hip stems, which represent the current standard of care for cementless revision hip arthroplasty and are CE-marked (Plasmafit^®^ Revision cup, Structan^®^ Augment, and Prevision^®^ Revision stem system, Aesculap, Tuttlingen, Germany). These implants are widely used in clinical practice and have established safety and performance profiles for hip arthroplasty revision.

Patients in the investigational group will receive IP-coated cementless acetabular cups, augments, and hip stems (Plasmafit^®^ Revision cup, Structan^®^ Augments, and Prevision^®^ Revision stem) during their revision hip arthroplasty procedure. Patients in the comparator group will receive non-IP-coated implants that are otherwise identical in design and mechanical properties to the investigational devices. All implants will be used in accordance with the manufacturer’s surgical manual and clinical guidelines. The surgical procedure will follow standard practices for revision hip arthroplasty, including preoperative planning, intraoperative implant positioning, and fixation. Patients can only be included if both the acetabular and femoral prostheses are exchanged, and the investigational devices are suitable for the revision procedure. Articulation options, including a modular dual mobility option, may be chosen according to patient-specific and surgical factors. The selection of implant sizes and components will be based on preoperative imaging and intraoperative assessment of patient anatomy and bone defects.

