All analyses will be based on the eligible randomized patient population. A CONSORT diagram will be used to visualize the number of participants screened, randomized, treated, and analyzed for the primary outcome. Secondary analyses will be exploratory. Secondary analyses will be performed without confirmatory character:Functional outcome and quality of life in the treatment groups between treatment arms will be evaluated using a linear regression model with repeated measures.Two-year implant survival will be evaluated according to the Kaplan-Meier [6] method and compared in the treatment arms with log-rank test for the events. ◦ Periprosthetic joint infections as defined for the primary endpoint◦ Septic revisions◦ All-cause revisionsRadiological outcome in the treatment groups for the endpoints◦ Implant migration▪ Occurrence of hip stem migration > 2 mm by using a logistic regression model with repeated measures▪ Radiological signs of loosening▪ Mean migration in patients with relevant migration (> 2 mm) by using a linear regression model with repeated measures ◦ Radiologic changes in the fixation area▪ Occurrence of any radiolucency by using a logistic regression model with repeated measures Safety outcomes of adverse events, device failure, and component revision between treatment arms will be evaluated by using a logistic regression.

Silver ion concentrations in peripheral blood and drainage fluid will be descriptively analyzed.

Results of statistical tests are evaluated using a *p*-value. The significance level is set to 5% two-sided and 2.5% one-sided, respectively. Two-sided 95% confidence intervals may be given in addition.

SAS VIYA 4 statistical software (SAS Institute Inc., Cary, NC, USA) or an adequately suited alternative will be used to generate the analysis datasets and to perform statistical calculations. The R package rpact from CRAN is used to calculate the combination of tests for primary analysis.

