### Interim analyses {21b}

Three interim analyses are planned:Interim analysis I will be conducted after the pilot phase for safety assessment of the 6 weeks’ results of part A subjects. All AEs of the safety population will be summarized for the analysis. Where applicable, descriptive statistics may be used based on AE categories. No analysis of the primary endpoint, secondary performance, or other variables will be performed.Interim analysis II is planned for the purpose of sample size re-estimation. The sample size re-estimation will be performed if either the first 134 patients have passed their 12-month follow-up time point or when more than 90% of the subjects of the initially calculated sample size (242 or more subjects) have been treated, whatever happens first. The interim analysis is performed based on unblinded data, because the effect size and the events in the control group cannot be reliably predicted. No confirmatory test is carried out during interim analysis II (i.e., no early efficacy or futility stop).The interim analysis III includes analyses of primary and secondary efficacy endpoints, based on the intention-to-treat population. The primary endpoint analysis will be conducted as soon as the 12-month follow-up period of the stage 2 patients is completed.

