### Methods in analysis to handle protocol nonadherence and any statistical methods to handle missing data {20c}

The primary analysis will follow the intent-to-treat (ITT) principle, including all eligible randomized participants in the groups they were assigned. A per-protocol (PP) analysis will be conducted as a sensitivity analysis, excluding participants with significant protocol deviations.

Statistical methods (e.g., multiple imputation) for handling missing values are not used. In the case of a partial date such as adverse event onset date or date of death, the unknown portion of the date of the event will be imputed. If the month and year are known, the 15th of the month will be used for analysis. If only the year is known, the event will be analyzed as if it occurred on June 30 of the known year. In the rare case that the date is fully unknown, the date will be imputed as the operation date.

Dropout reasons will be carefully documented to assess potential biases.

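### A blanket rule puts every analysis on the eligible randomised population, which does not fit the safety population named for interim analysis I and leaves safety and silver results without an implant-received basis

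*Protocol article*

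**What the plan says.** Section {20a} of the protocol article gives one general rule: "All analyses will be based on the eligible randomized patient population". It then lists the analyses. For safety: "Safety outcomes of adverse events, device failure, and component revision between treatment arms will be evaluated by using a logistic regression". For silver: "Silver ion concentrations in peripheral blood and drainage fluid will be descriptively analyzed". Neither is exempted from the rule.

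Two other sections point elsewhere:

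- Interim analyses {21b}, on the part A safety look: "All AEs of the safety population will be summarized for the analysis". The same section ties the intention-to-treat set to efficacy: "The interim analysis III includes analyses of primary and secondary efficacy endpoints, based on the intention-to-treat population".
- Section {20c} states grouping by assignment for the primary analysis only: "The primary analysis will follow the intent-to-treat (ITT) principle, including all eligible randomized participants in the groups they were assigned". The one alternative set that it names is per protocol: "A per-protocol (PP) analysis will be conducted as a sensitivity analysis, excluding participants with significant protocol deviations".

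On whether assigned and received implants can differ:

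- Table 1 places randomisation at −7 to −2 and implantation at 0. Section {16c} also has randomisation requested before the operation.
- Section {11b} allows for the assigned intervention to be changed or stopped.

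**The concern.** Analysis of all eligible randomised patients is the right basis for the efficacy test. For harm the usual basis is the patients who were implanted, grouped by what was put in. Argyria and blood silver depend on the device in the body, not on the allocation list.

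The article lists evaluation of device safety among its objectives {7}, and argyria and silver levels among its outcomes {12}. If the blanket sentence governs these results, three things could follow:

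- A patient allocated to the coated device but given a standard implant would count as coated and dilute the arm.
- A patient allocated to the comparator but given a coated part would have any silver finding reported under the comparator.
- Patients randomised but never implanted would stay in the safety denominator.

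The blanket sentence also makes it unclear whether the part A safety look and the final safety analysis use the same patients. An analysis plan with an as-received safety set would contradict {20a} as it stands, so the conflict cannot simply be left to that document.

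**Working it through.** **1. The article's own figures.** The point rests on no stated figure, but the group sizes used below come from Sample size {14}, so they were checked first. The inputs are 21.5% against 8.6%, one-sided α = 0.025 and power 80%. With the pooled-variance formula and mean rate 0.1505:

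n = [1.960·√(2·0.1505·0.8495) + 0.842·√(0.215·0.785 + 0.086·0.914)]² / 0.129² ≈ 119.4, so 120 per group and 240 in total, as stated. For 10% drop-out, 240/0.90 = 266.7, so 267; the article has 268 (134 per arm). These figures reproduce.

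**2. The passages side by side.**

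| Place | Analysis | Population | Grouping |
|---|---|---|---|
| {20a} | all, including safety and silver | eligible randomised | not stated for safety or silver |
| {21b}, interim I | adverse events, part A | safety population | not stated |
| {21b}, interim III | efficacy endpoints | intention to treat | not stated |
| {20c} | primary | all eligible randomised | as assigned |

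The first two rows conflict on the population for adverse events. By-assignment grouping is explicit only in the last row.

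**3. Effect of grouping safety by allocation.** Let c1 be the share of the coated arm given uncoated implants, c2 the share of the uncoated arm given coated ones, and pT and pC the true harm risks with coated and uncoated implants. If departures are unrelated to risk:

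- coated arm as allocated: (1 − c1)·pT + c1·pC
- uncoated arm as allocated: (1 − c2)·pC + c2·pT
- difference: (1 − c1 − c2)·(pT − pC)

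The article gives neither departure rates nor harm rates, so every entry below is an assumption. The example takes a harm of 15% coated against 5% uncoated, 120 per arm, two-sided 5%.

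| c1 | c2 | Share of difference kept | Seen as | Difference (points) | Power |
|---|---|---|---|---|---|
| 0 | 0 | 1.00 | 15.0% v 5.0% | 10.0 | 0.74 |
| 2% | 0 | 0.98 | 14.8% v 5.0% | 9.8 | 0.72 |
| 5% | 0 | 0.95 | 14.5% v 5.0% | 9.5 | 0.70 |
| 10% | 0 | 0.90 | 14.0% v 5.0% | 9.0 | 0.66 |
| 5% | 5% | 0.90 | 14.5% v 5.5% | 9.0 | 0.64 |
| 10% | 10% | 0.80 | 14.0% v 6.0% | 8.0 | 0.54 |

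For scale, 5% of 134 is 6.7 patients. For an effect that only silver can cause, assumed at 5% against 0%, the uncoated arm would show 0.05 × 5% = 0.25% at c2 = 5%, and nothing at c2 = 0.

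**The case against.** The strongest reply is that {20a} says who is analysed, not how safety patients are grouped. Grouping by assignment is written only for the primary analysis. The article plainly expects more than one analysis set: it names a safety population, and {17b} speaks of analysis populations in the plural. The definition of that set, and the rule for mixed constructs, may well be in the full protocol or the analysis plan. This much stands: by-allocation grouping of safety is the natural reading of a comparison between treatment arms, but it is an inference, and the missing definition is no fault of the article. What the reply does not remove is the word *All* in {20a} set against {21b}.

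Several stronger readings are tempting, and the article does not support them:

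- *Components are chosen during surgery, so coatings will be swapped.* The sentence in {6b}, "The selection of implant sizes and components will be based on preoperative imaging and intraoperative assessment of patient anatomy and bone defects", concerns fit to anatomy and bone defects. The comparator is described as the same design without the coating, so choosing another size or adding an augment does not require a change of coating. The devices also differ visibly {17a}, which makes accidental swaps less likely.
- *Swaps run both ways.* Section {11b} mentions standard treatment as the alternative. That points mainly from coated to uncoated, so the one-way rows of the table are the more relevant ones.
- *The two safety looks are known to differ in basis.* The safety population is not defined in the article, so a difference is possible but not shown.
- *By-allocation grouping always hides harm.* It attenuates only if departures are unrelated to risk. Selective departures could bias either way, and the as-received comparison is then confounded too.
- *Silver must be tabulated by component.* A descriptive analysis does not preclude this, and it is a preference rather than a correction.

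**Conclusion.** The point holds as a conflict of wording with a conditional consequence. Section {20a} states a rule that literally covers adverse events, device failure, component revision and silver, while {21b} uses another population for adverse events. Received and assigned implants can differ, because randomisation comes first and changes to the assigned intervention are foreseen.

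If safety is then grouped by allocation, the loss of a true harm difference is c1 + c2 as a share: 2% to 10% over the one-way rates assumed above, up to 20% with 10% departures in both directions, and zero with none. This rests on assumed departure and harm rates and on departures unrelated to risk. The safety analyses are exploratory, and the primary test and sample size are unaffected. It is not shown that harm will be diluted in this trial or that silver effects will be credited to the wrong arm.

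**What to change.** - In {20a}, limit the sentence on the eligible randomised population to efficacy and performance analyses.
- Add that adverse events and adverse device effects, device failure, component revision, argyria, safety laboratory values and silver levels are analysed in the safety population, meaning all implanted patients, by implant actually received. Any coated component counts as coated.
- Use the same set at interim analysis I and in the final analysis, and say so in {21b}.
- Keep the by-allocation safety table as supportive. The as-received comparison is not protected by randomisation and may be confounded if intraoperative difficulty drives departures.

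The cost is wording in the protocol and, where needed, the analysis plan. The sample size does not change. It also relies on recording, for each patient, which implanted components were coated. Settling the wording before safety data accumulate avoids a later choice of safety set that could look data-driven.

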### Outcomes {12}

The primary endpoint is the infection-free survival rate, evaluated to demonstrate that revision hip implants with the antimicrobial silver coating significantly reduce the rate of periprosthetic reinfections within 12 months after hip revision arthroplasty. The primary variable is the occurrence of periprosthetic joint infection classified as “infection likely” or “infection confirmed” according to the European Bone and Joint Infection Society (EBJIS) criteria [11]. The time point for assessing this outcome is 12 months postoperatively, as the silver coating is designed to provide efficacy within this period. 

Secondary endpoints will be functional outcomes assessed using the Harris Hip Score (HHS) [14], focusing on pre- and postoperative scores to determine improvements in hip functionality, as well as quality of life evaluated through the EQ-5D-5L questionnaire [15]. Further, Kaplan-Meier implant survival will be determined for endpoints including septic revisions and all-cause revisions. Radiological outcome (hip stem migration, radiological signs of loosening, radiologic observations in the fixation area) will be evaluated using standardized X-rays. Safety outcomes including device failure, signs of systemic or local argyria, and (S)AEs and (S)ADEs will be documented. In addition, specific laboratory parameters related to liver (ALT, AST, GGT) and kidney (eGFR) function, as well as inflammatory markers (e.g., CRP, leukocytes), silver ion in peripheral blood and drainage liquid, and surgery-related data, including bone defect classification, length of stay, and antibiotic therapy details will be evaluated.

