## Statistical methods

### Statistical methods for primary and secondary outcomes {20a}

The primary endpoint of this study is the comparison of infection-free survival rates (periprosthetic infections) within 12 months after revision total hip arthroplasty (THA) due to periprosthetic joint infection. The following hypothesis will be tested:H₀ (null hypothesis): hT ≥ hCHₐ (alternative hypothesis): hT < hC

where hT represents the hazard function in the treatment group and hC represents the hazard function in the control group for the 12-month postoperative period.

The primary null hypothesis is tested using a one-tailed inverse normal combination test at *α* = 0.025, allowing for a two-stage adaptive study design that combines log-rank tests for each stage. The null hypothesis is rejected if the combined *p* < 0.025. The *p*-values for each stage (*p*₁ and *p*₂) will be calculated using a one-sided log-rank test for periprosthetic reinfections (as defined by EBJIS criteria) within 12 months post-treatment. Kaplan–Meier survival curves will be right-censored at 12 months.

Descriptive statistics or comparative analyses between the treatment and control groups for demographic data, safety, and performance variables will be conducted where appropriate. Functional outcome and quality of life in the treatment groups between treatment arms will be evaluated using a linear regression model with repeated measures. Two-year implant survival will be evaluated according to the Kaplan-Meier method and compared in the treatment arms with log-rank test for the events periprosthetic joint infections, septic revisions, and all-cause revisions. Occurrence of any radiolucent line, and occurrence of hip stem migration > 2 mm will be analyzed by using a logistic regression model with repeated measures, as well as the mean migration in patients with relevant migration (> 2 mm) by using a linear regression model with repeated measures. Safety outcomes of adverse events, device failure, and component revision between treatment arms will be evaluated by using a logistic regression.

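### The linear model for stem migration is restricted to patients who migrated more than 2 mm, so its between-arm difference is not a randomised comparison (minor; one exploratory radiological result)

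*Protocol article*

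**What the plan says.** The section on statistical methods for primary and secondary outcomes {20a} gives the analysis twice. The running text has "as well as the mean migration in patients with relevant migration (> 2 mm) by using a linear regression model with repeated measures". The list of secondary analyses repeats it under implant migration as "Mean migration in patients with relevant migration (> 2 mm) by using a linear regression model with repeated measures".

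Four other statements bear on how it should be read:

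- The same list plans a companion analysis that is not restricted to migrators: "Occurrence of hip stem migration > 2 mm by using a logistic regression model with repeated measures".
- The general rule on population in {20a} is "All analyses will be based on the eligible randomized patient population".
- The status of the whole list is "Secondary analyses will be performed without confirmatory character".
- Outcomes {12} places migration with the radiological results: "Radiological outcome (hip stem migration, radiological signs of loosening, radiologic observations in the fixation area) will be evaluated using standardized X-rays". Safety is a separate item: "Safety outcomes including device failure, signs of systemic or local argyria, and (S)AEs and (S)ADEs will be documented".

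The article describes no comparison of mean migration in all randomised patients.

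**The concern.** Randomisation makes the two arms comparable as wholes. It does not make the coated patients who migrated more than 2 mm comparable with the control patients who did so. If the coating affects migration at all, it also affects who enters this subset, and the treatment coefficient then mixes the effect on the amount of migration with a change in who is counted.

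Suppose the coating moved some stems from below 2 mm to just above it. Those small values would join the coated arm's average and pull it down, so the arm with more migration could show the lower mean. Section {20a} says that test results are judged by p-value at 5% two-sided, so such a coefficient could carry a nominal p-value in the wrong direction. The restriction also fits poorly with the general statement that analyses rest on the randomised population.

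**Working it through.** **What can be reproduced.** The plan gives no sample size, SD or effect for migration. The only size to borrow is the primary-endpoint figure in Sample size {14}. With 21.5% against 8.6%, one-sided alpha 0.025, 80% power and the pooled-variance chi-square formula without continuity correction, the result is 120 per group (power 80.2%), as stated. Allowing for dropout, 120/0.9 = 133.3, rounded up to 134 per group, or 268. The 120 per arm serves below only to scale the illustrations.

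**All migration distributions below are assumptions.** For each, compare the all-patient mean with the mean among patients above 2 mm.

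*1. Simple arithmetic example.* Control: 90% at 0.8 mm, 10% at 6 mm. Coated: 80% at 0.8 mm, 10% at 2.5 mm, 10% at 6 mm.

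- All patients: control 0.9×0.8 + 0.1×6 = 1.32 mm; coated 0.8×0.8 + 0.1×2.5 + 0.1×6 = 1.49 mm. Coated is worse by 0.17 mm.
- Above 2 mm only: control 6.0 mm; coated (2.5 + 6)/2 = 4.25 mm. Coated looks better by 1.75 mm.
- Occurrence above 2 mm: 10% control, 20% coated. Coated is worse.

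*2. Plain shift.* For a normal variable with mean μ and SD σ, put a = (2 − μ)/σ. The share above 2 mm is 1 − Φ(a), and the mean above 2 mm is μ + σφ(a)/(1 − Φ(a)).

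| Assumed distribution | Share > 2 mm, control / coated | All-patient means (mm) | Means above 2 mm (mm) |
|---|---|---|---|
| Normal, SD 1, mean 0.5 / 1.0 | 6.7% / 15.9% | 0.50 / 1.00 | 2.44 / 2.53 |
| Lognormal, log-SD 0.8, median 0.8 / 1.3 | 12.6% / 29.5% | 1.10 / 1.79 | 3.19 / 3.66 |

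The direction is kept in both. The difference shrinks from 0.50 to about 0.09 mm in the normal case, and from 0.69 to 0.47 mm in the lognormal case.

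*3. Excess of moderate migrators, with spread.* Stable stems average 0.7 mm, moderate migrators lie at 2–3 mm (mean 2.5) and severe migrators at 4–6 mm (mean 5). Control: 90% stable, 5% moderate, 5% severe. Coated: 75% stable, 20% moderate, 5% severe.

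- All patients: control 0.90×0.7 + 0.05×2.5 + 0.05×5 = 1.005 mm; coated 0.75×0.7 + 0.20×2.5 + 0.05×5 = 1.275 mm.
- Above 2 mm only: control (0.125 + 0.25)/0.10 = 3.75 mm; coated (0.50 + 0.25)/0.25 = 3.00 mm.

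*4. Simulation of case 3 and a milder case.* There were 5,000 trials with 120 per arm and one value per patient. A t-test and a two-proportion z-test stand in for the repeated-measures models, at 5% two-sided.

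| Coated arm (control 5% moderate, 5% severe) | Restricted mean favours coated | Significantly so | Occurrence shows significant harm | All-patient mean shows significant harm |
|---|---|---|---|---|
| 20% moderate, 5% severe | 95% | 44% | 88% | 47% |
| 15% moderate, 6% severe | 86% | 22% | 65% | 34% |

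In these cases the restricted mean and the occurrence analysis usually disagree, and the occurrence analysis is the one that compares the randomised groups.

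**The case against.** The strongest reply is that the plan does not rest on the restricted mean. The logistic model for migration above 2 mm covers all patients with radiographs, and in the scenario that produces reversal it detects the harm more often than an all-patient mean does (88% against 47%). Example 1 shows the same ordering. Occurrence of 10% against 20% has power of about 58% with 120 per arm. The all-patient difference of 0.17 mm, with SDs of about 1.56 and 1.59, has a standard error of about 0.20, z of about 0.84 and power of about 13%. Reporting how many migrated and by how much among those who did is a recognisable two-part description, and limiting the second part to relevant migration avoids noisy small readings. This stands as a reason to keep the logistic model as the main comparison. It does not make the restricted coefficient a randomised comparison.

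The article could also be read as leaving the radiological comparison descriptive, because the list says only that these outcomes are evaluated in the treatment groups. That is possible. But a regression model is named, it stands among models that compare arms, and the section says that tests are judged by p-value.

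A reader might infer three stronger things, and the documents support none of them:

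- *That a safety conclusion could be reversed.* Outcomes {12} lists migration as radiological. The safety analyses in {20a} are of adverse events, device failure and component revision, each separate from this model.
- *That the plan as a whole hides harm.* The occurrence model would show the excess migrators, and signs of loosening, radiolucency and all-cause revision also bear on fixation.
- *That reversal is to be expected.* It needs an excess of moderate migrators in one arm. A plain shift only attenuates, and no migration data are given from which to judge which pattern is likelier.

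**Conclusion.** The point holds in a limited form, and its severity is minor. That the comparison selects on its own outcome after randomisation follows from the wording alone and needs no distributional assumption. The size of the distortion does need one: attenuation from 0.50 to about 0.09 mm, or reversal from 1.01 against 1.28 mm to 3.75 against 3.00 mm, are illustrations under assumed distributions and simplified one-visit tests.

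What is affected is one exploratory radiological result on fixation. The primary result and the named safety outcomes are untouched. Exploratory status lowers the stakes, but it does not make the coefficient interpretable as an effect of the coating.

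**What to change.** 1. Keep the logistic model for migration above 2 mm, and name it as the main migration comparison.
2. Fit the repeated-measures linear model to migration in all randomised patients with radiographs.
3. Report the mean among patients above 2 mm by arm as description, with the number of patients, next to the occurrence result and without a between-arm test.

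The cost is a change of wording in the analysis plan. Table 1 already schedules the radiographs for every participant, so no new data are needed. The downside is that readings below 2 mm carry more measurement noise, so the all-patient mean may be less sensitive than the occurrence analysis. That is why the latter should lead.
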